## 6.4 Study procedures

|                              | Screening                              | Informed consent procedure       | Baseline assessment | Surgery                                               | 4 weeks follow up              | 3 months follow up                                                              | 6 months follow up                                                              |
|------------------------------|-----------------------------------------------|-----------------------------------------|----------------------------|--------------------------------------------------------------|---------------------------------------|----------------------------------------------------------------------------------------|----------------------------------------------------------------------------------------|
| Clinician/ researcher | Identify eligible patients with hip fractures | Explain PIF, answer questions, sign ICF | DHFA*                      | Record implant details
Record complications               |                                       | Standard clinical follow up, including DHFA                                            | Standard clinical follow up                                                            |
| Researcher            | Identify eligible patients with hip fractures | Answer additional questions if needed   | - DHFA
- EQ-5D          | Screen surgical report for relevant information if necessary | Health care utilization questionnaire | - EQ-5D
- FES-1 scale
- NRS
- SPPB
- Health care utilization questionnaire | - EQ-5D
- FES-1 scale
- NRS
- DHFA
- Health care utilization questionnaire |
| Patient/ proxy        |                                               | Read PIF, ask questions, sign IC        | Complete questionnaire     |                                                              | Complete questionnaire                | - Complete questionnaires
- SPPB at outpatient clinic                               | Complete questionnaires                                                                |

\*DHFA is a registry used in standard care includes: living status, pre-mobility score, KATZ, ASA, complications, discharge destination, re-operations

When hospitals are participating with this trial, treating physicians will be asked to screen if patients admitted to the hospital with a hip fracture are eligible for study entry. If inclusion criteria are met, they can contact the research coordinator by phone (☎ ([contact]) or visit the trial website, for further assistance with obtaining informed consent, randomisation and inclusion of the patient.

To obtain informed consent, the patient information letter will be handed out to eligible patients or to their health care proxy. Hard copies will be available in all participating hospitals or could be found as a download on the trials' website.

Hip fractures are injuries where treatment is required in less than 48 hours for optimal outcomes. Therefore, the time in which patients can consider if they are willing to participate to the study, is limited to the time until surgery. Informed consent of patients in the Natural Experiment can be obtained after surgery. The research coordinator will contact these patients.

For patients with severe cognitive impairment due to dementia, informed consent will be obtained by their health care proxy. It is to the doctors' opinion to determine if a patient

has a cognitive impairment. When the diagnosis is not clear, a clinical geriatric doctor will be consulted

### **Randomisation**

After obtaining informed consent at the emergency department or patient ward, patients will be randomly assigned in a 1:1 allocation ratio to one of the following study arms:

- Treatment with a cemented hemiarthroplasty using the DLA
- Treatment with a cemented hemiarthroplasty using the PLA

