### **6.2 Randomisation, blinding and treatment allocation**

Eligible patients admitted to the hospitals where both surgical techniques are practiced, are invited for participating in our RCT prior to the surgery. When patients agree to participate, written informed consent will be obtained and patients will be randomised between the PLA and the DLA. Randomisation will be stratified per center and per orthopaedic/trauma surgeon. Randomisation will be done in CASTOR EDC, a secured study and data management system with built-in randomisation (variable block method).

Surgeons, patients or outcome assessors cannot be blinded since the different surgical approaches are easily distinguishable (i.e. based on the location of the scar).

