### 6.3 Natural Experiment

Alongside the RCT we will conduct a natural experiment in hospitals with surgeons who are only comfortable (or competent) in performing one of the two surgical approaches. Allocation to treatment using the PLA or DLA is determined by the hospital where the patient is admitted to (i.e. by the topographical location where the trauma takes place). These natural factors are outside the control of the investigators, resembling random assignment. Patients in the natural experiment are invited for participating after surgery, and informed consent will be obtained for follow-up and data usage.

We will recruit participating centers based on surgical expertise balancing number of centers based on surgical approaches used.

Although we are aware this is not a formal randomization on participant level, the NE design has several advantages(22):

- Most importantly, we will prevent surgical expertise bias.
- The NE design will facilitate better generalizability of our trial results since more centers are able to participate. Generalizability will help implementing our trials results.
- We will be able to reduce selection bias, by including patients and surgeons who may not have agreed to randomisation.

Interventions to prevent other forms of bias:

- Selection bias: We will be able to compare the RCT and NE results with anonymous data from the DHFA registry that includes all patients who were treated for hip fractures in the participating centers.
- Detection bias: Patients participating in our study will be blinded to the study hypothesis.
- Attrition bias: Follow-up will be performed by a research coordinator assuring completeness of data.
- Reporting bias: We will publish our study protocol in an open access peer reviewed journal and at [www.clinicaltrials.gov](http://www.clinicaltrials.gov)
- Performance bias: The Dutch Hip Fracture Guideline introduced in 2015 will prevent performance bias since treatment protocols are standardised apart from the surgical approach used. Hip fracture guideline adherence is good (23).

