## **6.7 Follow-up of subjects withdrawn from treatment**

If patients – for whatever reason – do not undergo the allocated treatment, this will be recorded as protocol deviation. Withdrawing from the randomized treatment is not a reason to terminate study participation, because follow up data of these patients are needed for intention-to-treat analyses. Therefore, patients will be invited for the study follow up measurements, and details of the treatment they received instead of the randomized procedure will be recorded. Subjects will be invited for all follow up measurements as described in this protocol, except those who explicitly withdraw informed consent.

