### **9.2 Recruitment and consent**

Every patient with a hip fracture which should be treated with a hemiarthroplasty will be invited for study entry. Information will be given through the patient information letter and patients are able to ask questions to the treating physician or investigator. Their consent will be asked by the treating physician. In case of incapacitated subjects (i.e. elderly with cognitive impairment such as dementia), informed consent will be received by proxy through the legally representative or a family member. A copy of the signed informed consent form will be given to the patient/proxy as a separate document together with the patient information letter. Until the moment of surgery, patients will have the time to reconsider their decision. Normally, patients with hip fractures are treated in 24 hours after admission to the emergency room.

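### The allocation is drawn before surgery and not withheld, while patients may still reconsider; an avoidable, possibly arm-related loss of the primary outcome follows

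*Protocol*

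**What the plan says.** On the order of events, Protocol 6.2 states: "When patients agree to participate, written informed consent will be obtained and patients will be randomised between the PLA and the DLA". Section 6.4 (Randomisation) repeats it and names the setting: "After obtaining informed consent at the emergency department or patient ward, patients will be randomly assigned in a 1:1 allocation ratio". Neither section ties the draw to a later point such as arrival in theatre.

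On blinding, 6.2 states: "Surgeons, patients or outcome assessors cannot be blinded since the different surgical approaches are easily distinguishable (i.e. based on the location of the scar". The only masking of patients is in 6.3: "Patients participating in our study will be blinded to the study hypothesis". That concerns the hypothesis, not the arm.

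On changing one's mind, 9.2 states: "Until the moment of surgery, patients will have the time to reconsider their decision". Section 6.5 also allows a subject to leave at any time and for any reason.

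On follow-up, 6.7 records a patient who does not undergo the allocated approach as a protocol deviation and still invites that patient to all measurements for the intention-to-treat analysis, "except those who explicitly withdraw informed consent". Section 6.6 does not plan to replace withdrawn subjects, because a 25% loss is already expected.

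**The concern.** The decision to take part stays open after the allocation has been drawn, and nothing prevents the patient or proxy from learning the arm in that interval. Someone who prefers the other approach can then withdraw consent because of the draw. No 6-month EQ-5D-5L will exist for that person, so analysing by allocated arm cannot restore the comparison.

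Nothing else in the protocol recovers the value. Section 6.5 keeps data collected before withdrawal, which is at most a baseline EQ-5D-5L. The DHFA comparison in 6.9 collects age, gender, ASA, BMI, cognitive impairment and date of death, but no quality of life. The natural experiment (6.3) runs in hospitals whose surgeons use one approach only. The GEE model in 8.1 cannot supply the missing outcome, and an unweighted GEE relies on data missing completely at random, which withdrawal driven by the arm would violate.

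What is at stake is mainly bias in the primary comparison. The target difference is small (0.08), and a larger sample does not remove bias.

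**Working it through.** **Sequence, section by section**

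1. Consent in the emergency department or ward, then the draw (6.2, 6.4).
2. Arm not masked, and no step withholds it before surgery (6.2; 6.3 masks the hypothesis only).
3. Reconsideration allowed until surgery (9.2).
4. Patient declines the allocated approach: stays in follow-up (6.7).
5. Patient explicitly withdraws consent: no follow-up (6.7), no replacement (6.6).

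The gap is therefore confined to step 5.

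**The plan's own figure (4.4)**

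Inputs: difference 0.08, SD 0.3, two-sided alpha 0.05, power 80%, loss 25%, total 610.

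- Normal approximation: n = 2 × (1.960 + 0.842)² × 0.3² / 0.08² = 221 per arm. The t-test version gives 221.7, so 222, as stated.
- Inflation for loss: 444 / 0.75 = 592. The stated 610 is 18 higher.
- Evaluable at 25% loss: 610 × 0.75 = 457.5, or 228.75 per arm. Power = Φ(0.08 / (0.3 × √(2/228.75)) − 1.960) = 81.4%.

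**Effect on power**

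The protocol gives no rate of withdrawal between draw and surgery. Assume a further 2%, 5% or 10% on top of the 25%.

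| Further loss | Both arms: n per arm | Both arms: power | One arm only: power |
|---|---|---|---|
| 2% | 224.2 | 80.6% | 81.0% |
| 5% | 217.3 | 79.4% | 80.4% |
| 10% | 205.9 | 77.2% | 79.3% |

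If these withdrawals fall within the 25% allowance instead, no planned power is lost.

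**Effect on bias**

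Let w be the share of one arm that leaves, and D the mean EQ-5D of stayers minus that of leavers. The full-arm mean is (1 − w) × stayers + w × leavers, so the observed mean of that arm is off by w × D. With no such loss in the other arm, this is the bias in the difference. Both w and D are assumptions. The second figure in each cell is the share of the 0.08 MCID.

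| w | D = 0.08 | D = 0.15 | D = 0.30 |
|---|---|---|---|
| 2% | 0.0016 (2.0%) | 0.0030 (3.8%) | 0.0060 (7.5%) |
| 5% | 0.0040 (5.0%) | 0.0075 (9.4%) | 0.0150 (18.8%) |
| 10% | 0.0080 (10.0%) | 0.0150 (18.8%) | 0.0300 (37.5%) |

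The sign of D is unknown, so the bias could favour either approach.

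**The case against.** The strongest reply is that the protocol already handles the main route. A patient who dislikes the arm can decline the approach and remain in the trial under 6.7. Patients do not know the hypothesis (6.3), and both techniques are in wide use (9.4), so the motive to leave may be weak. The documents give no evidence that such withdrawals happen. All of this stands. It limits the size of the problem but does not close the route through withdrawn consent.

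Several stronger readings are tempting, and the documents do not support them:

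- *The arm is openly known at consent.* The draw follows consent, and no section says when, or whether, the patient is told. The reason given for not blinding is the scar, which exists only after surgery. The text supports only that the arm is not withheld.
- *A day or more separates the draw from surgery.* The 24 hours in 9.2 run from admission, and the 48 hours in 6.4 concern timely treatment. Neither measures the interval from draw to surgery, which is shorter by the time needed for screening and consent.
- *Section 6.4 also lets patients reconsider after the draw.* Its wording, "the time in which patients can consider if they are willing to participate to the study, is limited to the time until surgery", is most naturally read as time to decide before consenting. Only 9.2 speaks of reconsidering.
- *This is the only loss that can depend on the arm.* It is not. Section 1 expects more dislocation after one approach and more abductor insufficiency after the other, so loss after surgery can differ too. What sets this loss apart is that it precedes any treatment and can be avoided.
- *The trial would be underpowered.* Even a further 10% loss in both arms leaves 77.2%, and a one-sided 10% leaves 79.3%.

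There is also a fair practical objection. The two approaches use different patient positions (5.1), so a late draw gives theatre less time to prepare and could itself cause deviations.

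**Conclusion.** The point holds as a cheap improvement to procedure. No stated figure is wrong and no sections contradict each other, and the right to withdraw is not in question. The weakness is an unmasked draw placed inside a period in which participation may still be reconsidered.

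The size cannot be derived from the protocol. The range of about 2% to 38% of the MCID rests on three assumptions: 2% to 10% of one arm leave, they differ from stayers by 0.08 to 0.30, and the other arm has no such loss. The upper end needs both a one-sided 10% withdrawal and a difference nearly four times the MCID, so it is an outer bound for illustration and not an expectation.

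**What to change.** Amend 6.2 and 6.4 (Randomisation) as follows:

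- Keep consent in the emergency department or ward. Release the CASTOR allocation as close to surgery as logistics allow, after consent and eligibility have been re-confirmed and the operating surgeon is known. The surgeon is a stratification factor in 6.2, so late release also fits the stratification.
- If late release is not workable at a centre, at least do not disclose the arm to the patient or proxy before surgery.
- Count patients who change their minds before release as not randomised, under 6.9.
- Record the release time, and report withdrawals between randomisation and surgery by arm, separately from patients who declined the allocated approach but stayed in follow-up.

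The cost is a short amendment and a change to the randomisation work instruction, with no extra staff or visits. The downside is that the theatre team learns positioning and instrument needs later, so each centre should settle the latest workable release point. Withdrawals after surgery are not affected by this change.

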### **Baseline assessment**

At baseline we will assess the EQ-5D-5L, the ADL functionality (KATZ), pre-mobility score and the living status using the Dutch Hip Fracture Audit (DHFA) registration. The assessment of the above outcomes is based on the health status prior to the trauma.

### **Surgery**

All operations will be performed by experienced surgeons or residents under the direct supervision of an experienced surgeon. Antibiotic and tromboembolic prophylaxis and wound dressing are done according to the judgment of participating surgeon and local guidelines. The surgical report will be available to the research team in order to extract any relevant information on the procedure. Hospital protocols and guidelines will be followed regarding physical therapy and rehabilitation program, and will be recorded. The DHFA will be completed after surgery and after check-up in the outpatient clinic.

### **Follow-up data collection**

The baseline and follow-up assessment will be conducted by the coordinating research team of the OLVG. There are three follow-up moments at 4 weeks, 3 and 6 months postoperative. The primary outcome measurement EQ-5D-5L and the secondary outcomes FES-I scale will be assessed through questionnaires online, by hardcopy or by phone at baseline, 3 and 6 months postoperatively. The health care utilization questionnaire will be assessed at 4 weeks, 3 and 6 months follow-up. The questionnaires will be handed out by the coordinating researcher. Other secondary outcome measurements (e.g. KATZ, mobility score, complications, re-operations) are detailed in the DHFA at baseline and 3 months post-operatively and will be assessed through questionnaires online, by hardcopy or by phone at 6 months after surgery and will be handed out by the coordinating researcher.

The assessment of the Short Physical Performance Battery (SPPB) balance test, which is not included in the DHFA, will be performed by one of the study researchers or nurse practitioner to protect continuity and feasibility and will only be assessed in patients included in the RCT. The SPPB will not be assessed in all patients, but in a subgroup of the patient population because the sample size is smaller. The SPPB is a group of measures that combines the results of the gait speed, chair stand and balance tests.(24)

The follow-up questionnaires will contain:

- Health-related quality of life as measured by the EQ-5D questionnaire. The EQ-5D-5L is a descriptive system of health-related quality of life states consisting of five dimensions (mobility, self-care, usual activities, pain/discomfort and anxiety/depression)(25).
- The Katz Index of Independence in Activities of Daily Living, the Katz ADL, is an instrument to assess functional status as a measurement of the client's ability to perform activities of daily living independently consisting six functions (bathing, dressing, toileting, transferring, continence and feeding)(26).
- The Falls Efficacy Scale-International (FES-I) is a short, easy to administer tool that measures the level of concern about falling during social and physical activities inside and outside the home whether or not the person actually does the activity(27).
- Additionally injuries as a result of falling and other (indication to) re-interventions
- Mobility is assessed by the Pre-fracture Mobility scale, which is specific for hip fracture patients. The scale represent patients with no need for any walking aid and no restriction in walking distance to patients who are bedbound(28).
- Pain as measured by a eleven-point Numeric Rating Scale(29).
- Health care resources utilization (including amongst others, number of visits to the general practitioner and use of home care organizations)

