## SUMMARY

**Rationale:** In the Netherlands the two main surgical approaches for hemiarthroplasty are the posterolateral and the direct lateral approach. Currently there is no conclusive evidence which of these two approaches results in better patient outcomes.

**Objective:** Assessing the patient outcome comparing the posterolateral with the direct lateral approach in patients being treated with cemented hemiarthroplasty after femoral neck fractures.

**Study design:** A randomised controlled multi-center superiority trial and natural experiment with an economic evaluation alongside.

**Study population:** All patients older than 18 years with a femoral neck fracture whereby treatment with cemented hemiarthroplasty is recommended according the national guidelines.

**Intervention:** Treatment with cemented hemiarthroplasty using the posterolateral approach.

**Standard intervention to be compared to:** Treatment with cemented hemiarthroplasty using the direct lateral approach.

**Main study parameters/endpoints:** The primary outcome is the patient-rated quality of life (EQ-5D-5L) at 6 months after surgery.

Secondary outcomes are: ADL functionality (KATZ), Balance test (SPPB), Tendency to Fall (FES-I), Pain (NRS), Re-interventions, Mobility, Discharge destination, Complications, and cost-effectiveness.

**Nature and extent of the burden and risks associated with participation, benefit and group relatedness:** The different approaches in the two treatment arms of the randomised controlled trial are widely used techniques in the Netherlands and many of the outcome measures are part of the standard clinical follow-up after hip fracture. Therefore, there is no extra risk or burden for participating patients, except for the time to complete some additional follow-up measurements. The primary outcome measurement and secondary outcomes, will be assessed through questionnaires online, by hardcopy or by phone at baseline, 3 and 6 months postoperatively. The assessment of the Short Physical Performance Battery (SPPB) balance test, will be performed by one of the study researchers or nurse practitioner to protect continuity and feasibility.

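### The protocol contradicts itself on whether FES-I is measured at baseline, and so on whether its change-over-time analysis starts at baseline or at 3 months

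*Protocol*

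**What the plan says.** Four places in the protocol bear on when FES-I is collected.

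- **Section 6.4, Follow-up data collection** groups FES-I with the primary outcome: "the secondary outcomes FES-I scale will be assessed through questionnaires online, by hardcopy or by phone at baseline, 3 and 6 months postoperatively".
- **Summary** makes a general statement to the same effect: "The primary outcome measurement and secondary outcomes, will be assessed through questionnaires online, by hardcopy or by phone at baseline, 3 and 6 months postoperatively".
- **Section 6.4, schedule table** lists only the DHFA and EQ-5D for the researcher at baseline. FES-I (printed as FES-1) appears at 3 months, "EQ-5D - FES-1 scale - NRS - SPPB - Health care utilization questionnaire", and at 6 months, "EQ-5D - FES-1 scale - NRS - DHFA - Health care utilization questionnaire". The footnote gives the registry content: "DHFA is a registry used in standard care includes: living status, pre-mobility score, KATZ, ASA, complications, discharge destination, re-operations".
- **Section 6.4, Baseline assessment** states: "At baseline we will assess the EQ-5D-5L, the ADL functionality (KATZ), pre-mobility score and the living status". It adds: "The assessment of the above outcomes is based on the health status prior to the trauma". FES-I is not among the measures named.

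On analysis, section 8.1 applies GEE models like the primary one to continuous secondary outcomes. Each includes a group-by-time interaction to assess whether the arms differ in their course over time.

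**The concern.** The protocol fixes the data collection for this outcome in two incompatible ways. This is not a detail left for a statistical analysis plan, because an analysis plan cannot supply a measurement that was not made.

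FES-I is the instrument named for tendency to fall. The Introduction, the efficiency section that follows it and section 9.4 all argue that abductor damage after the direct lateral approach may impair balance and raise the risk of falling. The outcome is secondary but close to the reason for the trial.

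Two things are at stake. First, the planned model is about change over time, and without a baseline its first time point is 3 months after surgery. Second, in the natural experiment (section 6.3) the approach follows from the admitting hospital. Patients of different hospitals may differ in prior concern about falling, and without a baseline value this could be neither examined nor adjusted for.

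**Working it through.** No figure in the protocol needs reproducing. The check is a side-by-side reading, followed by what each schedule means for the model.

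**Step 1. FES-I time points by source**

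| Place in protocol | Baseline | 3 months | 6 months |
|---|---|---|---|
| 6.4, Follow-up data collection | yes | yes | yes |
| Summary (secondary outcomes in general) | yes | yes | yes |
| 6.4, schedule table | not named | yes | yes |
| 6.4, Baseline assessment | not named | – | – |

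The follow-up text gives three time points and the table gives two.

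**Step 2. Can another baseline entry supply FES-I?** The DHFA cannot, because its listed items do not include it. The patient row of the table calls for a questionnaire at baseline without saying which. That leaves room for FES-I but does not establish it, since the researcher cell for the same visit names EQ-5D and not FES-I.

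**Step 3. Is the follow-up text a loose generalisation?** It does not read as one. The same paragraph gives the health care utilization questionnaire and the DHFA items their own, different time points, and it places FES-I with EQ-5D.

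**Step 4. What the section 8.1 interaction estimates.** Let D0, D3 and D6 be the between-arm differences in mean FES-I at baseline, 3 and 6 months.

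- Three time points: the interaction compares D3 − D0 and D6 − D0 with zero, that is, change from baseline.
- Two time points: the only contrast is D6 − D3.

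Take an illustrative case in which the arms start equal (D0 = 0) and differ by a constant d from 3 months on (D3 = D6 = d). With a baseline, the interaction contrasts are d − 0 = d at both visits. Without one, the contrast is d − d = 0. An effect already present at 3 months and then stable would not show in the interaction on the table's schedule. It would still show in the group term, so it is not lost to the model. It is lost to the term that the protocol singles out.

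**Step 5. Precision, as an assumption only.** The protocol gives no correlation r between baseline and 6-month FES-I. Adjusting for baseline reduces residual variance by r², equivalent to 1/(1 − r²) − 1 more evaluable patients for this outcome:

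- r = 0.2: 4% less variance, equivalent to 1/0.96 − 1 = 4% more patients
- r = 0.4: 16% less, equivalent to 1/0.84 − 1 = 19% more
- r = 0.6: 36% less, equivalent to 1/0.64 − 1 = 56% more

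The range is too wide to carry any weight. The contradiction stands without it.

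**The case against.** The strongest reply is that little may go wrong in practice. The protocol says that "The baseline and follow-up assessment will be conducted by the coordinating research team of the OLVG", and the coordinating researcher hands out the questionnaires. One central team, working under the paragraph that names FES-I at baseline, may well collect it. The table is also not exhaustive: number of falls and injuries from falling, both secondary outcomes in section 6.1.2, are not named in it. This stands. A reader might infer that sites will follow the table and that the baseline FES-I will certainly be missing. The documents show a risk, and it lies with the central team.

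A reader might also infer that the protocol promises a pre-fracture FES-I. It does not. The pre-trauma reference is stated only for the measures listed under Baseline assessment, and FES-I is not one of them. In the natural experiment, patients are invited after surgery, so a baseline FES-I would be a post-operative recall there, and its value for adjustment is less certain. Nor would a missed value be wholly beyond recovery, since the 4-week questionnaire offers an early contact, though again only by recall.

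The Summary is weak support. Its statement covers secondary outcomes as a whole, including complications and discharge destination, which have no meaningful baseline value.

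Finally, the table and the Baseline assessment text agree with each other. Removing the baseline FES-I from the follow-up text would therefore also restore consistency, and in the randomised comparison allocation already guards against systematic imbalance. Both points are right. They leave the contradiction in place and show that there are two ways to resolve it.

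**Conclusion.** The contradiction is real, and nothing elsewhere in the protocol resolves it. It goes beyond a clerical slip because it decides whether the FES-I model of section 8.1 covers change from baseline or only change from 3 to 6 months, and whether prior concern about falling can be examined in the natural experiment.

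The consequence is conditional on the research team working from the table. The matter is minor: it affects one secondary outcome and neither the primary outcome nor the sample size. A reader might infer a quantified loss of precision. The protocol supports none, because it gives no correlation for FES-I and does not state a baseline-adjusted analysis.

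**What to change.** Reconcile the Summary and, in section 6.4, the schedule table, the Baseline assessment text and the Follow-up data collection text. There are two consistent ways.

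1. **Preferred: collect it.** Add FES-I to the baseline column of the table and to the Baseline assessment text. State its reference period as pre-trauma, in line with the other baseline measures. Note that natural-experiment patients would answer by recall after surgery. Use the baseline value in the FES-I model. This matches what the follow-up text already promises and the change-over-time aim of section 8.1.
2. **If a baseline FES-I is not intended,** remove the baseline time point for FES-I from the follow-up text and align the Summary. State that the FES-I model compares the arms at 3 and 6 months and does not assess change from baseline.

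The first option costs protocol wording and a few minutes of questionnaire time per patient at an existing contact. That contact falls around admission for randomised patients and after surgery in the natural experiment. The second costs wording only, but it gives up any baseline check on FES-I in the natural experiment.
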